## 2. Materials and Methods

### 2.1. Design

This is a prospective, observational investigation designed to identify factors associated with treatment response and prognosis in a clinical anxiety group. The study population comprises two groups: individuals with anxiety disorders and a healthy control group. The anxiety group will complete assessments at baseline, 4 months, and 12 months, whereas the control group will undergo a single baseline assessment. The overall follow-up period is 12 months, with participant enrollment and data collection planned from 2024 through 2029.

Although no structured therapeutic intervention is administered as part of the research protocol, participants in the clinical anxiety group may receive naturalistic treatment-as-usual, including pharmacological or psychotherapeutic interventions, as determined by their treating clinicians. Accordingly, the study does not involve randomization, allocation concealment, or blinding procedures. The overall design and temporal structure of the study assessments are illustrated in Figure 1.

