### 2.3. Recruitment Process and Screening for Enrollment

The clinical anxiety group will be recruited through outpatient psychiatric clinics at Samsung Kangbuk Hospital, where attending psychiatrists will identify individuals who meet the inclusion criteria. The healthy control group will be recruited via public announcements on institutional bulletin boards.

To confirm eligibility and psychiatric status, all participants will be evaluated by a board-certified psychiatrist using structured diagnostic interviews. The Structured Clinical Interview for DSM-5 Disorders will be used to verify diagnoses in the clinical anxiety group [27], while the Mini International Neuropsychiatric Interview (MINI) 5.0.0 will be administered to screen for comorbid conditions or to confirm the absence of psychiatric history in healthy controls [28].

All eligible participants will receive a detailed explanation of the study’s purpose, procedures, potential risks, and their rights. Written informed consent will be obtained before any assessments are conducted. Participation is entirely voluntary, and individuals may withdraw at any time without affecting their clinical care.

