#### 2.5.1. Clinical Assessments

Clinical assessments will be conducted at the baseline and 12-month follow-up for all participants. Each session will be administered by a board-certified psychiatrist or trained research personnel. The assessment will include the collection of sociodemographic variables such as age, sex, education level, marital status, occupation, alcohol use, smoking status, height, and weight. Additionally, a structured evaluation of psychiatric history will be performed, including the onset and duration of anxiety symptoms, previous psychiatric diagnoses and treatments (treatment type, dosage, duration), and family history of psychiatric disorders.

These data will provide essential contextual information for interpreting behavioral, physiological, and neuroimaging findings, and for exploring clinical predictors of treatment response and prognosis. Some of these data will also be used as independent variables in the analysis.

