#### 2.5.2. Evaluation of Anxiety Symptoms and Associated Psychiatric Conditions

To comprehensively assess anxiety and related cognitive-affective constructs, multiple validated self-report measures will be administered. Each instrument serves a distinct role within the analytic framework. Key clinician-rated and self-report instruments include the Panic Disorder Severity Scale (PDSS), the Depression Anxiety Stress Scales-21 (DASS-21), the Generalized Anxiety Disorder-7 (GAD-7), the Intolerance of Uncertainty Scale (IUS), and the Anxiety Sensitivity Index-Revised (ASI-R). Each instrument serves a distinct analytic role within the study framework. The PDSS functions as the primary measure of panic-related symptom severity and behavioral avoidance and is used to define treatment response. The DASS-21 Anxiety subscale serves as a secondary outcome reflecting generalized physiological and cognitive anxiety, while the GAD-7 provides a complementary index of generalized worry and assists in screening for comorbid anxiety presentations. The IUS and ASI-R act as mechanistic predictors, capturing cognitive and interoceptive vulnerability dimensions that contribute to anxiety maintenance.

Neurocognitive functioning will be evaluated using the CNS Vital Signs battery, while stress exposure will be assessed using the Stress and Adversity Inventory. Affective states will be measured using the Positive and Negative Affect Schedule (PANAS), which assesses momentary affective experiences across two dimensions: positive and negative affect. The Behavioral Inhibition and Activation Systems (BIS/BAS) scales will be included to evaluate motivational and affect-regulatory tendencies. These measures contribute to the RDoC Arousal and Regulatory Systems domain, capturing interindividual variability in emotional and motivational responsiveness.

To reduce participant burden and ensure longitudinal feasibility, shortened versions of selected questionnaires will be administered at interim visits (2 and 12 months). Remote administration via telephone or a secure institutional online platform may be employed as appropriate. All remote procedures will use validated formats and standardized instructions to maintain reliability and data comparability across timepoints. Detailed descriptions of each instrument—including theoretical constructs, administration procedures, psychometric properties, and language validation—are provided in the Supplementary Material (Table S1).

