### 2.6. Outcomes and Operational Definitions

The primary outcome of this study is treatment response, operationally defined as a clinically meaningful reduction in panic symptom severity. Responders are defined as participants who achieve a ≥40% decrease in the total score of the PDSS from baseline to each follow-up assessment (2, 6, and 12 months), while participants not meeting this criterion are classified as non-responders.

This threshold was selected based on prior evidence indicating that a 35–45% decrease on disorder-specific anxiety scales corresponds to clinically meaningful improvement and early treatment benefit [30,31]. The 40% criterion also provides adequate sensitivity for detecting within-subject improvement across multiple timepoints in longitudinal designs.

To ensure conceptual coherence with the study’s transdiagnostic framework, additional analyses will examine changes in the GAD-7, DASS-21 Anxiety subscale, and LSAS as secondary outcomes, and the consistency of responder classification across these measures will be evaluated. This multi-metric approach retains sensitivity to panic-specific reactivity while enabling comparability with broader anxiety-disorder literature.

These operational definitions allow for both categorical classification (responder vs. non-responder) and continuous modeling of symptom change, facilitating the integration of clinical, behavioral, physiological, and neuroimaging predictors across the 12-month follow-up.

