## 4. Benefits and Risks to Participants

This study involves minimal risk, as it is based on non-invasive and observational procedures. However, certain assessments may cause temporary discomfort or psychological distress. Participants may experience mild anxiety during clinical interviews or VR-based behavioral tasks that simulate stress-inducing situations. Additional discomfort may arise from the application of EEG/ECG sensors, potential motion sickness during VR exposure, or feelings of claustrophobia during MRI scanning.

To mitigate these risks, participants will be fully informed in advance about all procedures and potential discomforts. They will be allowed to take breaks or discontinue specific assessments at any point. A trained clinician or research staff member will be present throughout all study procedures to monitor participant well-being and respond promptly if distress arises.

Participation in this study may provide benefits such as access to a comprehensive psychiatric evaluation and enhanced insight into one’s psychological health. Participants in the clinical anxiety group will also receive longitudinal follow-up, which may contribute to self-monitoring and inform future clinical care. While no therapeutic intervention is provided within the research protocol, information gathered during the study may support personalized treatment planning.

Participation is entirely voluntary. Individuals may withdraw at any time without consequence to their current or future medical care. If needed, participants will be referred for appropriate clinical services.

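### Section 2.1 rules out all blinding for a reason that covers only treatment, so nothing masks PDSS raters to the baseline markers being tested as predictors of response

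*Protocol article*

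**What the plan says.** Section 2.1 says that "participants in the clinical anxiety group may receive naturalistic treatment-as-usual, including pharmacological or psychotherapeutic interventions, as determined by their treating clinicians", and then draws the consequence: "Accordingly, the study does not involve randomization, allocation concealment, or blinding procedures".

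The primary outcome is in section 2.6: "Responders are defined as participants who achieve a ≥40% decrease in the total score of the PDSS from baseline to each follow-up assessment", with follow-up at 2, 6 and 12 months. Section 3.3 sets out to predict this label from sociodemographic, clinical, VR, EEG/ECG, skeletal and imaging features.

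On who rates the outcome, section 2.5.2 opens by describing the measures as self-report, then uses a mixed label: "Key clinician-rated and self-report instruments include the Panic Disorder Severity Scale (PDSS". Administration details are referred to Supplementary Table S1, which is not shown.

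On use of the data in care, section 4 says that "information gathered during the study may support personalized treatment planning". Section 6 restricts the electronic data to authorised study staff. Section 3.3 records medication and psychotherapy and allows them to enter as covariates or as predictors, depending on the modelling aim. Section 7 names ongoing treatment as a possible confounder. It does not mention rater knowledge of the markers.

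**The concern.** Having no allocated treatment settles one kind of blinding only. In a study that evaluates baseline markers as predictors, the person who assigns the outcome should not know the predictor values. Section 2.1 removes both kinds of blinding in one sentence, for a reason that bears on the first kind alone.

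Two routes could then produce an association between marker and response that does not reflect prognosis:

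- **Rating.** A rater who saw a patient react strongly in the VR elevator, or who knows a marker result, may score the follow-up PDSS differently and move patients across the 40% line.
- **Treatment.** A released marker result may influence the treatment given, so that the marker predicts response through the care it prompted.

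The k-fold or nested cross-validation in section 3.3 and the bootstrap in section 3.4 reuse the same labels. They assess stability and overfitting and cannot reveal a label that is biased in every fold.

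**Working it through.** No sample size, power or alpha in the article depends on this point, so there is no stated figure to reproduce. The check is a reading of the text followed by an illustration of size.

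**Reading**

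1. The absence of blinding is stated outright in section 2.1, so it is not merely a detail left to a fuller document.
2. The section 4 sentence excludes no type of data. It permits marker feedback without scheduling it.
3. Section 6 limits who can open the coded data. Authorised study staff may include PDSS raters or treating psychiatrists, and nothing says otherwise.
4. Staff can see the VR reaction directly: "A trained clinician or research staff member will be present throughout all study procedures". Patients come from clinics "where attending psychiatrists will identify individuals who meet the inclusion criteria". No separation of care, marker acquisition and outcome rating is stated.

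**Illustration A: rating bias with a continuous marker of no true value**

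Inputs: response 75%, from the 25% non-response assumed in section 2.7. The SD of PDSS change (5 points, varied from 4 to 7) and the shift b in points per marker SD are assumptions; the article gives neither.

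- P(response | marker m) = Φ(0.674 + b·m/SD), where Φ(0.674) = 0.75 and m is standard normal.
- AUC = P(marker of a random responder > marker of a random non-responder), by numerical integration over m.

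| SD | b | Share of ratings affected | AUC |
|---|---|---|---|
| 5 | 0.5 | all | 0.55 |
| 5 | 1.0 | all | 0.59 |
| 5 | 1.5 | all | 0.64 |
| 4 | 1.0 | all | 0.62 |
| 7 | 1.0 | all | 0.57 |
| 5 | 1.0 | 25% | 0.52 |
| 5 | 1.0 | 10% | 0.51 |

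For a partial share s, the response probability is s·Φ(0.674 + b·m/SD) + (1 − s)·0.75.

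For a median-split marker with a shift of ±1 point at SD 5, response is Φ(0.674 + 0.2) = 80.9% versus Φ(0.674 − 0.2) = 68.2%.

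**Illustration B: a net shift in response by either route, binary marker at 50% prevalence**

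Completers: 145 × 0.8 = 116, so 58 per marker group. Response is 75% + d versus 75% − d, and AUC = 0.5 + (sensitivity − false-positive rate)/2. For d = 5 percentage points:

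- sensitivity = 0.5 × 0.80/0.75 = 0.533
- false-positive rate = 0.5 × 0.20/0.25 = 0.400
- AUC = 0.5 + 0.133/2 = 0.57

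| d (percentage points) | AUC | Chance of p < 0.05 |
|---|---|---|
| 2.5 | 0.53 | 9% |
| 5 | 0.57 | 24% |
| 10 | 0.63 | 71% |

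Here d is an average over all patients. A 10-point shift confined to a quarter of them is a net 0.25 × 10 = 2.5 points, which is the first row.

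**The case against.** The case against has real force on several points.

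- **Section 4 is a general benefits statement.** A reader might infer that the study plans to feed EEG, VR or MRI results to treating clinicians. It does not say so: the sentence says only that information may support planning, names no marker, and follows remarks on psychiatric evaluation and follow-up. Feedback is permitted, not planned.
- **Access is already limited.** Section 6 keeps the data from clinicians who are not study staff. This narrows the treatment route but does not close it, because raters or treating psychiatrists may themselves be authorised.
- **The PDSS rater is unsettled.** A reader might infer from the mixed label that the PDSS is clinician-rated. Section 2.5.2 does not establish this. If it is self-reported, the rating route would need participants to learn their own results.
- **Shared staffing is not documented.** A reader might take the statement "Each session will be administered by a board-certified psychiatrist or trained research personnel" to mean that the same people run the VR session and rate the PDSS. That sentence stands in section 2.5.1, where the content described is sociodemographic and psychiatric-history collection. The article is silent on who does both.
- **Most markers cannot be read at the visit.** EEG, MRI and skeletal features come out of processing pipelines, and no direction is specified in advance. Visible distress in VR is the realistic exposure for a rater.
- **Treatment is recorded.** If a marker acts only through recorded treatment, conditioning on treatment blocks that path, absent unmeasured confounding of treatment and outcome. Section 3.3 leaves that adjustment optional, and it does nothing for rating bias.

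These points limit reach and size. None supplies a reason for leaving raters unmasked to the predictors.

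**Conclusion.** The point holds in a limited form. Section 2.1 excludes all blinding for a reason that does not cover masking of outcome raters to the baseline markers, and no other section provides it. The rating route depends on the PDSS being clinician-rated. The treatment route depends on marker results being released, which section 4 allows and section 6 only restricts.

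The size cannot be derived from the article. Under the assumed 1-point shift per marker SD, an uninformative marker would show an AUC of about 0.57 to 0.62 if every rating were affected. The more plausible case of a minority of affected ratings gives about 0.51 to 0.52 at SD 5. The documents do not show that the results will be biased, only that the design as stated leaves a preventable opening. The exploratory label in section 3.4 does not remove it, since a spurious marker would still be carried forward as a hypothesis. This is a cheap improvement, best made early: data collection runs to 2029, and later analysis cannot undo what a rater already knew.

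**What to change.** 1. In section 2.1, state that no treatment is allocated, but that PDSS raters are masked to baseline VR, EEG/ECG, skeletal-tracking and MRI data and, where existing staffing allows, did not run that participant's VR session. State whether the PDSS is clinician-rated or self-reported.
2. State that research-derived marker features are not routinely released to raters or treating clinicians before the participant's last outcome is recorded. Exempt safety and incidental findings.
3. Reconcile the section 4 sentence on treatment planning with this, and set access rights under section 6 to match.
4. Log any release, and repeat the main analysis without the participants concerned.

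The cost is protocol and consent wording, some rostering of existing staff, access settings on a data store that is already coded, and one sensitivity analysis. The downside is that participants and clinicians receive research feedback later.

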### 2.2. Eligibility Criteria

Participants will be assigned to either the clinical anxiety group or the healthy control group according to the following inclusion and exclusion criteria:

#### 2.2.1. Inclusion Criteria

The inclusion criteria for the clinical anxiety group are (1) adults aged between 19 and 60 years; (2) currently diagnosed with an anxiety disorder based on DSM-5 criteria, specifically including panic disorder, SAD, GAD, agoraphobia, or specific phobia, confirmed by a board-certified psychiatrist (individuals who have been previously treated for anxiety are not included); (3) ability to understand the purpose and procedures of the study and provide written informed consent, and (4) no history of major neurological disorders or psychotic illness.

The inclusion criteria for the healthy control group are (1) adults aged between 19 and 60 years; (2) no current or past psychiatric diagnoses and not currently using any psychotropic medication; and (3) ability to fully understand the purpose and procedures of the study and provide written informed consent.

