#### 2.2.2. Exclusion Criteria

The exclusion criteria for the clinical anxiety group are (1) inability to read or understand the consent form; (2) significant difficulty using VR equipment (e.g., due to visual or vestibular impairment); (3) history of epilepsy, brain injury, or other neurological disorders; (4) severe physical illnesses (e.g., cancer, active tuberculosis, cardiovascular disease); (5) currently diagnosed with substance use disorder or alcohol use disorder (nicotine use will not be excluded); (6) presence of pacemakers or implanted metallic devices; (7) pregnancy or belonging to a legally or socially vulnerable population (e.g., institutionalized individuals or employees of the research facility); and (8) individuals who had previously completed a structured treatment protocol for anxiety within the past six months.

All exclusion criteria listed above apply to the healthy control group as well, with the addition of any previous or current psychiatric disorder.

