### 3.3. Predictive Modeling of Treatment Response

The primary objective is to develop machine-learning models that predict treatment response (≥40% PDSS reduction at 2, 6, and 12 months). Binary (responder vs. non-responder) and three-group models (healthy control, responder, non-responder) will be evaluated. Predictor features will include sociodemographic and psychiatric-history variables, clinical and psychometric scores, VR-derived behavioral indices, EEG/ECG features, 3D skeletal tracing, and neuroimaging markers. In most models, age and sex will be treated as basic covariates given their known influence on neural and behavioral measures. Lifestyle variables (e.g., education, smoking, alcohol use) and treatment-related clinical variables (medication use and psychotherapy) will be systematically recorded and incorporated either as covariates to adjust for treatment effects or as candidate predictive features, depending on the specific modeling objective and analytic context.

Predictor inclusion and feature reduction will be guided by a combination of theoretical relevance and empirical criteria. Candidate variables will undergo an initial screening based on prior literature and clinical interpretability. Dimensionality will then be reduced using data-driven feature-selection procedures, such as penalized regression methods (e.g., LASSO) or feature-importance-based ranking, with the number of retained features determined by model performance and stability rather than a predefined target. Variables exhibiting substantial multicollinearity (e.g., variance inflation factor > 5), redundancy, or consistently low contribution across cross-validation folds may be excluded prior to model fitting.

All features will be standardized, and missing values handled using multiple imputations by chained equations or similar robust approaches. Depending on data characteristics, dimensionality-reduction techniques (e.g., principal component analysis) may be applied before model fitting.

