This study has several methodological and practical limitations. First, the longitudinal design is asymmetric: healthy controls are assessed twice (baseline and 12 months), whereas the anxiety group is followed three times (2, 6, and 12 months), limiting short-term trajectory comparisons. Second, ongoing medication and psychotherapy may confound treatment-response estimates, although these variables will be recorded and statistically adjusted. Third, combining multimodal data (VR, EEG, ECG, MRI) entails potential synchronization errors, variable signal quality, and data-loss risks. Standardized preprocessing and quality-control pipelines have been implemented, but residual heterogeneity may remain. Finally, practical issues such as participant burden, VR sensitivity, and attrition could affect data completeness and generalizability. Despite these constraints, the protocol emphasizes reproducibility and transparent analytic procedures to support robust, hypothesis-generating findings on neurobehavioral predictors of treatment response. In summary, this protocol outlines a longitudinal, multimodal investigation designed to identify neurobehavioral predictors of treatment response in individuals with anxiety disorders. By aligning clearly defined outcomes with standardized acquisition and analysis pipelines across behavioral, physiological, and neuroimaging domains, the study aims to generate reproducible, mechanistic insights into the processes underlying anxiety improvement. The inclusion of harmonized procedures, cross-modal synchronization, and transparent analytic workflow diagrams ensures methodological rigor and clarity, thereby facilitating future replication and data sharing within the field.

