## Figures and Tables

**Figure 1 jcm-15-00007-f001:**
[figure not shown]
Study flowchart showing enrollment, allocation, follow-up, and analysis for both the clinical anxiety group and healthy control group. Participants in the clinical anxiety group received treatment-as-usual (e.g., pharmacotherapy or psychotherapy) as prescribed by their clinicians. Treatment response was defined as a ≥40% reduction in Panic Score Severity Scale (PDSS) scores at follow-up. No intervention was administered by the study team.

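### Entry rules conflict on prior anxiety treatment, and neither the response label nor the predictor rule ensures that PDSS change reflects a treatment begun after baseline

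*Protocol article*

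**What the plan says.** **Entry.** The inclusion criteria (section 2.2.1) state that "individuals who have been previously treated for anxiety are not included", with no time limit and no restriction by type of treatment. Exclusion criterion (8) (section 2.2.2) removes "individuals who had previously completed a structured treatment protocol for anxiety within the past six months". The Discussion (section 7) lists as a limitation that "ongoing medication and psychotherapy may confound treatment-response estimates", and adds that these variables will be recorded and adjusted for.

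**Treatment during follow-up.** Section 2.1 says that "participants in the clinical anxiety group may receive naturalistic treatment-as-usual". The Figure 1 legend states it as fact: "Participants in the clinical anxiety group received treatment-as-usual (e.g., pharmacotherapy or psychotherapy) as prescribed by their clinicians".

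**Outcome.** Section 2.6 defines a responder as a participant whose PDSS total falls by at least 40% from baseline at 2, 6 and 12 months. It sets no condition on receiving or starting treatment.

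**Predictors.** The Abstract describes models built from baseline multimodal features. Section 3.3 promises systematic recording of treatment variables, namely medication and psychotherapy. Their use is left flexible: "incorporated either as covariates to adjust for treatment effects or as candidate predictive features". The choice rests with the aim of each model. The section does not say at what time these variables must be known.

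**The concern.** The study's product is a model that uses baseline information to predict treatment response. Three things have to be fixed for that claim to be clear: whether patients are untreated at baseline, whether the label refers to patients who received treatment, and whether every predictor is known at baseline. The article leaves each of them open.

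- **Baseline state.** If some patients enter on treatment, their baseline EEG, heart-rate variability and MRI may reflect that treatment. Controls may not be taking psychotropic medication (section 2.2.1). The imaging group comparisons in section 3.2 name only age and sex as covariates, and section 3.4 adds medication status only as needed.
- **Label.** Among untreated patients, a 40% fall reflects natural course or regression to the mean, yet it is recorded as treatment response.
- **Predictors.** Treatment chosen or changed after baseline can be a reaction to early non-response. If it is used to predict status at 6 or 12 months, the model may appear to predict from baseline when it is partly reading the early course.

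**Working it through.** The plan gives no figure on this point, so the first three steps compare the text. The fourth is an illustration.

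**1. The two entry rules side by side**

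| Anxiety treatment before entry | Inclusion rule, 2.2.1 | Exclusion (8), 2.2.2 |
|---|---|---|
| None | admitted | not excluded |
| Structured protocol completed within six months | barred | excluded |
| Structured protocol completed longer ago | barred | not excluded |
| Structured protocol started, not completed | barred | not excluded |
| Unstructured treatment, past or continuing at entry | barred on a literal reading | not excluded |

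A participant must meet every inclusion criterion and no exclusion criterion. Applied literally together, the two rules give the population of the 2.2.1 column, and exclusion (8) removes nobody who is not already removed. Exclusion (8) has work to do only if some previously treated patients were meant to be admissible. So either it is void, or the inclusion text is not the intended rule. The word ongoing in section 7 does not settle this, because it could mean treatment continuing at entry or treatment during follow-up.

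**2. Label against treatment**

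Treatment is optional in section 2.1 and stated as received in the Figure 1 legend. The label in section 2.6 depends on PDSS alone. An untreated patient with a fall of at least 40% is therefore a treatment responder, and an untreated patient without one is a treatment non-responder.

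**3. Predictor timing**

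- If 2.2.1 holds literally, nobody has had anxiety treatment before entry. Anxiety medication and psychotherapy variables would then mostly describe what happened after baseline.
- If exclusion (8) is the working rule, treatment at entry could be a genuine baseline feature.

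Section 3.3 does not separate the two. Under the first reading, the permission for treatment as a candidate feature sits badly with the Abstract's description of baseline features.

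**4. Illustration of how many labels could be affected**

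Inputs from section 2.7: 145 patients, 20% dropout, and a reported remission range of 38–75%, used here as a stand-in for response among treated patients. Assumptions, not in the documents: untreated share u = 10–50%, and response without treatment r_u = 10–30%.

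- Completers: 145 × (1 − 0.20) = 116.
- Untreated responders = 116 × u × r_u. Low: 116 × 0.10 × 0.10 = 1.2. High: 116 × 0.50 × 0.30 = 17.4.
- Treated responders = 116 × (1 − u) × r_t.
- Smallest share of all responders (u = 0.10, r_u = 0.10, r_t = 0.75): 1.16 / (1.16 + 78.3) = 1.5%.
- Largest share (u = 0.50, r_u = 0.30, r_t = 0.38): 17.4 / (17.4 + 22.04) = 44%.

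The range runs from negligible to serious, and nothing in the article narrows it.

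**The case against.** The strongest reply has four parts.

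- **The entry rules can be applied.** Since both must be satisfied, the stricter one governs and the weaker one is redundant. Eligibility is confirmed by a psychiatrist at one hospital. This stands as far as it goes: the text does not show that treated patients will be enrolled or that baselines will be medicated. It does not remove the doubt about intent, because an exclusion with no effect suggests that a different population was in mind.
- **The study is openly naturalistic and exploratory.** Section 3.4 lists medication status and treatment type as potential covariates, and section 7 discloses confounding by treatment. This also stands, so it would be too strong to say that PDSS change cannot be read as response. But the disclosure covers neither the entry conflict nor untreated responders, and covariate adjustment does not change a patient's label.
- **Leakage is not shown.** No sentence says that post-baseline treatment will enter a baseline model. That is correct. The point is that section 3.3 permits it by setting no time limit.
- **Recording is promised.** A reader might infer from section 2.5.1, which says that "Clinical assessments will be conducted at the baseline and 12-month follow-up for all participants" and includes "previous psychiatric diagnoses and treatments (treatment type, dosage, duration", that treatment is captured only at those two visits. The documents do not support this. Sections 3.3 and 7 promise recording without limiting it to two visits, and the assessment schedule in Figure 2 is not shown. Nor does that history item contradict section 2.2.1, since it covers psychiatric treatment generally and can include treatment for other conditions.

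**Conclusion.** The point holds in this form: the entry rules on prior treatment are incompatible and must be reconciled, and the article does not ensure that PDSS change reflects a treatment begun after baseline. Section 3.3 also leaves room for post-baseline treatment among the predictors of a baseline model.

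The textual findings rest on no assumption. Their size does. The article states neither how many patients will be untreated nor how many might enter on treatment. The illustration of about 1 to 17 untreated responders, or 1.5% to 44% of all responders, depends on the assumed untreated share and untreated response, and on using remission as a stand-in for response. It shows sensitivity and is not an estimate.

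A reader might go on to infer that the primary analysis should be limited to patients who start treatment after baseline. That does not follow. It would condition on an event after baseline, give a model for a subgroup that cannot be identified at baseline, and shrink an already small sample.

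**What to change.** 1. Reconcile section 2.2.1, exclusion (8) in section 2.2.2 and the limitation in section 7 into one statement on prior and ongoing anxiety treatment. This review takes no view on which rule is right. Align section 2.1 and the Figure 1 legend on whether treatment is optional.
2. In section 3.3, allow only treatment variables known at baseline as predictors in the baseline models. Use later treatment descriptively or in sensitivity analyses.
3. Keep all patients in the primary prediction analysis. Add a sensitivity analysis with separate reporting by treatment status: untreated, treated at entry, started after baseline.
4. To support this, record treatment start and stop dates at the visits already held. Enrolment and data collection run from 2024 through 2029, and such dates are harder to reconstruct later, particularly for patients who drop out.

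The cost is a wording change, slightly more data entry and one further set of analyses. Apparent model performance may be lower once post-baseline treatment is excluded, but it will then describe prediction from baseline.
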